##### Glycolipid metabolism outcomes

Fasting blood glucose (FBG), fasting insulin (FINS), and HOMA-IR are early-warning indicators of prediabetes (77), and blood lipid levels are core risk factors for coronary heart disease (78). FBG will be measured using the hexokinase method (Hitachi 7180 Biochemistry Analyzer, Japan); FINS by electrochemiluminescence immunoassay (ECLIA; Roche Cobas e601); and HOMA-IR will be calculated as [FINS (μU/mL) × FBG (mmol/L)] / 22.5 (79). Lipids will include total cholesterol (TC; CHOD-PAP), triglycerides (TG; GPO-PAP), HDL-C (direct method), and LDL-C (homogeneous direct method). All assays will be calibrated according to IFCC standards.

##### Inflammatory markers

High-sensitivity C-reactive protein (hs-CRP >3mg/L) indicates elevated atherosclerotic risk (80), while persistently high levels of interleukin-6 (IL-6) and tumor necrosis factor-alpha (TNF-α) promote atherosclerosis progression and cardiovascular disease (81). Hs-CRP, IL-6, interleukin-10 (IL-10), and TNF-α will be measured using magnetic particle chemiluminescence (Beckman Coulter Access kits) on the DXI 800 analyzer. Detection ranges and limits: hs-CRP 0.1–10mg/L (0.03mg/L), IL-6 1.5–500pg/mL (0.7pg/mL), IL-10 1.2–1000pg/mL (0.6pg/mL), TNF-α 1.7–1000pg/mL (0.8pg/mL). Each batch will include calibrators and quality controls (R² ≥0.995).

##### Adipokines

Elevated leptin promotes visceral fat accumulation and insulin resistance (82), whereas low adiponectin is associated with exacerbated metabolic dysfunction (83). The leptin-to-adiponectin ratio (LAR) will be calculated as leptin divided by adiponectin and used as an exploratory adipokine-balance index (84). Leptin and adiponectin will be measured by CMIA (Abbott ARCHITECT i2000SR), and LAR calculated directly. Detection ranges: leptin 0.1–100ng/mL (0.05ng/mL), adiponectin 1–30μg/mL (0.5μg/mL). Samples will be recentrifuged 5minutes before testing to remove precipitates. Assays will follow manufacturer instructions with strict incubation control (30minutes at 37°C).

### Participant timeline

This study will include two main assessment time points: baseline and post-intervention. The primary outcome, secondary outcomes, exploratory outcomes, and descriptive data will be collected at these time points. Each assessment phase will be completed within one week to minimize temporal variation in outcome measurement. For participants in the ES group, post-intervention VO_2_max assessment will be scheduled 48–72 h after the final completed intervention session, including any make-up session, and this interval will be recorded.

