#### Criteria for discontinuing or modifying allocated interventions

The intervention will be promptly discontinued if a participant encounters any serious adverse event (SAE), including exercise-induced palpitations, chest pain, or syncope, upon verification by the study medical team. Additionally, participants retain the entitlement to exit the study at any point without providing any reason.

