#### Strategies to improve adherence to interventions

Prior to intervention initiation, all personnel involved in implementation will receive standardized training and pilot testing from the study core team. Competency in intervention protocols, intensity control, and safety management will be verified through assessments while simultaneously evaluating program feasibility and safety. During the intervention period, adherence will be supported through standardized weekly WeChat reminders, instructor-recorded attendance, and prespecified make-up sessions where feasible. Make-up sessions will be arranged within the weekly training schedule and will not alter the prespecified post-intervention assessment window. The 5–6 person adherence groups will be used only for scheduling coordination and attendance reminders. These groups will not provide peer counselling, motivational coaching, competitive ranking, or additional social-support activities. All adherence-related contacts will follow standardized procedures and be recorded to minimize differential social-support effects (51). Post-intervention, strategies including health improvement reports, personalized training feedback, and monthly health advice dissemination will be implemented to facilitate long-term maintenance of health behaviors.

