##### Body composition

Body fat percentage is an independent predictor of metabolic syndrome and is positively associated with insulin resistance (63, 64). Body composition—including basal metabolic rate (BMR), body fat percentage (FAT%), fat-free mass (FFM), total body water (TBW), extracellular water (ECW), and intracellular water (ICW)—will be assessed using the Bodystat^©^ QuadScan 4000 (Bodystat Ltd, UK). Participants will rest for 15minutes before testing and avoid vigorous exercise, alcohol, food, and water intake for at least 2 hours. Measurements will be conducted supine with electrodes attached to standard sites, and participants will remain relaxed.

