### Statistical methods

All statistical analyses will be conducted in R (version 4.4.1). Continuous variables will be summarised as mean ± standard deviation (SD) or median [(IQR)], as appropriate, and categorical variables as n (%). Baseline characteristics will be described descriptively for the randomised sample.

The primary analysis will follow the intention-to-treat principle. The between-group effect on post-intervention VO_2_max will be estimated using analysis of covariance (ANCOVA), with group allocation as the fixed factor and baseline VO_2_max as the covariate. The primary treatment effect will be reported as the adjusted mean difference with a 95% confidence interval (CI), and statistical inference for the primary outcome will be based on a two-sided alpha level of 0.05. If meaningful between-group imbalance in recorded compulsory PE exposure is observed, a sensitivity analysis additionally adjusted for PE exposure may be conducted to examine the robustness of the primary findings.

Secondary and exploratory outcomes will be analyzed using analogous baseline-adjusted models. Psychological outcomes will be interpreted according to the prespecified hierarchy, with BDI and PSS prioritized as key secondary psychological outcomes. Outcomes with marked skewness will be analyzed using log-ANCOVA, with exponentiated estimates reported as geometric mean ratios and percentage differences. These outcomes will be interpreted as supportive or hypothesis-generating, with emphasis on effect estimates and 95% CIs rather than confirmatory hypothesis testing. Multiplicity considerations for prespecified secondary outcome domains will be addressed in the analysis hierarchy described for those outcomes.

Missing outcome data will be handled using multiple imputation with predictive mean matching, and estimates will be pooled using Rubin’s rules. The imputation model will include group allocation, the corresponding baseline outcome value, and relevant baseline predictors. A completers-only analysis will be performed as a sensitivity analysis. All tests will be two-sided.

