Several limitations warrant careful consideration. The sample size calculation was informed by ES-related VO_2_max evidence from a small RCT in sedentary obese college students. Greater VO_2_max variability in the broader sedentary university student population may reduce the actual statistical power. Eligibility screening based on self-reported IPAQ data may introduce assessment bias in physical activity and sedentary-time classification. The ≥6 h/day sedentary-time criterion was based on dose–response evidence from middle-aged and older adults and was applied to the present university-student sample by extrapolation. Anthropometric measures, including BMI and waist circumference, will be reported as baseline health characteristics rather than used to verify physical activity or sedentary behavior. Device-based verification of sedentary behavior and free-living physical activity is not planned in the present trial, which may increase the risk of sedentary-time misclassification and undetected activity contamination or co-intervention. The 12-week intervention period overlapping with final examination weeks may cause irregular training intervals or adherence fluctuations due to academic stress, although post-intervention VO_2_max assessment will be standardized according to the final completed intervention session. As a short-term study, the 12-week observation window might not fully capture the longer-term effects of ES, necessitating extended follow-up periods to assess effect persistence.

Despite these limitations, if supported, this trial would provide preliminary evidence on a structured stair-climbing ES protocol for sedentary university students and help clarify whether changes in CRF are accompanied by psychological and adherence-related responses. Subsequent studies should incorporate wearable sensors, including triaxial accelerometers, to improve sedentary-time classification and objectively quantify movement patterns. Such data may help examine whether intervention effects differ across BMI categories. Future studies should further examine personalized exercise dosing, dose-response relationships, comparative efficacy of diverse exercise snack formats, and combined interventions integrating ES with mindfulness-based practices.

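### For ES participants who stop training early, the two timing rules for the post-intervention VO2max test cannot both be met, and the 48–72 h rest interval protects no other outcome

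*Protocol article*

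**What the plan says.** Under Participant timeline, the article sets two assessment points, baseline and post-intervention, and adds: "Each assessment phase will be completed within one week to minimize temporal variation in outcome measurement". The next rule covers one arm and one outcome: "For participants in the ES group, post-intervention VO_2_max assessment will be scheduled 48–72 h after the final completed intervention session". A make-up session can serve as that last session, and the gap is to be documented. The Discussion repeats the anchor when it deals with training disrupted by examinations: "post-intervention VO_2_max assessment will be standardized according to the final completed intervention session".

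Under Strategies to improve adherence to interventions, make-up sessions "will not alter the prespecified post-intervention assessment window", so a fixed window is assumed to exist. Under Study design, controls attend the same scheduled assessments.

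Under Statistical methods: "The primary analysis will follow the intention-to-treat principle". The model is ANCOVA on post-intervention VO2max. Missing outcomes are multiply imputed from allocation, the baseline value and baseline predictors.

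Preparation for the other outcomes differs by measure:
- Body composition: participants must "avoid vigorous exercise, alcohol, food, and water intake for at least 2 hours".
- Blood pressure: advice against vigorous activity beforehand, with no duration.
- Blood sampling: a 10-hour fast and a draw between 7:00 and 9:00 AM, with no interval from exercise.
- Vital capacity and questionnaires: no interval stated.

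Compulsory PE classes are permitted and recorded in both arms.

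**The concern.** The VO2max rule counts from the last session a participant actually completed, not from the last one scheduled. The two coincide for anyone who trains to week 12 and separate for anyone who stops sooner. The article foresees such participants: it provides for discontinuation after a serious adverse event, free withdrawal, runs of missed sessions, 10% attrition and irregular training around examinations. They are also the participants for whom intention to treat matters, because their outcome should be measured at the same time as everyone else's. If two stated rules give different test dates for them, staff must choose, and only ES participants raise the choice.

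The second part concerns the other outcomes. The sponsor evidently judged that VO2max should not be measured soon after a session. The glucose, insulin, inflammatory and adipokine measures are meant to show pathways by which the intervention works, yet no similar separation is stated for them. A short-lived response to the last bout would then look like a 12-week adaptation.

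**Working it through.** **Inputs.** Training lasts 12 weeks (Intervention description). The test falls 48–72 h, that is 2–3 days, after the last completed session, and the assessment phase lasts one week (both Participant timeline). One assumption is added for illustration: the post-intervention phase is the seven days right after week 12. With day 1 as the first training day, that is days 85–91.

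**Formulas.** For a participant whose last session is at the end of week *w* (day 7*w*):
- literal test slot = day 7*w* + 2 to day 7*w* + 3
- days earlier than a week-12 completer = (12 − *w*) × 7
- gap since last session if tested in the common window = (85 − 7*w*) to (91 − 7*w*) days

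| Last session, end of week | Literal slot (day) | Days before a completer's slot | Inside days 85–91? | Gap if tested in days 85–91 |
|---|---|---|---|---|
| 12 | 86–87 | 0 | yes | slot falls in the window at 2–3 days |
| 11 | 79–80 | 7 | no | 8–14 days |
| 9 | 65–66 | 21 | no | 22–28 days |
| 6 | 44–45 | 42 | no | 43–49 days |
| 3 | 23–24 | 63 | no | 64–70 days |

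Week 12 satisfies both rules. The week 11 row depends on where the seven days are placed: days 80–86 would just hold both slots. For weeks 3, 6 and 9 no placement works, because the slots lie at least 21 days from a completer's and the phase lasts 7. Keeping the 2–3 day rule breaks the common window, and keeping the window breaks the 2–3 day rule.

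**What staff could do.** They could (a) test early, (b) test in the common window outside 48–72 h, or (c) treat the value as missing. Under (c) it would be imputed from allocation and baseline information; the stated model has no term for sessions completed. Recording the interval documents the departure but does not choose among these options.

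**Other outcomes against the 48 h standard.** Body composition requires 2 h. The blood pressure advice has no duration. For bloods only the fast and the draw time are fixed. As an illustration, a session ending at 17:00 the day before leaves 14 h to a 7:00 draw and 16 h to a 9:00 draw, and the text allows this. The order of the graded exercise test and the other measures within the week is not stated in the text either. That would affect both arms, whereas a recent trial session exists only in the ES arm.

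The sample size calculation does not depend on this point.

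**The case against.** The strongest reply is that a common window plainly exists. There are two assessment points, a one-week phase, make-up sessions that do not shift the window, and the same scheduled assessments for controls. On that view the 48–72 h rule only sets rest within the window. This largely stands. A reader might infer that early stoppers will be tested early, for example in week 5, while controls are tested after week 12. The documents do not support that as fact; it is one reading, and the common-window rules point the other way. What remains is that the interval rule has no exception for non-completers and the Discussion repeats it as the standard.

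On the other outcomes, it is fair to reply that some restrictions exist, that PE means recent exercise is not confined to the ES arm, that same-day exercise before a morning draw is unlikely, and that these outcomes are declared supportive or hypothesis-generating. All of this limits the concern without removing it: trial sessions occur in one arm only, and the previous day is not excluded.

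A reader might also infer that the test day reveals allocation to blinded technicians. Nothing in the article puts the arms on different days, and the Who will be blinded section restricts allocation records and bars questions about participation. That inference is unsupported.

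Finally, the schedule figure is not shown and may add timing detail.

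**Conclusion.** The point holds in limited form. First, two stated timing rules for the primary outcome conflict for any ES participant whose last session falls well before week 12, and the article does not say which prevails under an intention-to-treat analysis. Second, the rest interval protects VO2max alone, so residual effects of the last bout can enter secondary and exploratory outcomes, mainly in the ES arm.

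The gap in test dates can be computed: 21 to 63 days for stops at the end of weeks 9 to 3, taking whole weeks. The resulting bias cannot. A reader might try to size it by treating the 10% attrition allowance as the share tested early and assuming that part of the 3.5 mL/kg/min target is lost after stopping. The 10% inflates the sample size; it is not the proportion who stop training and still attend. The article gives no rate at which fitness is lost. The direction is open too: early testing could miss a later loss of fitness, catch incomplete adaptation, or miss time effects that controls carry to week 12. The acute effect on the other outcomes cannot be sized either.

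This should be corrected before post-intervention testing starts. It does not invalidate the design.

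**What to change.** Reconcile Participant timeline, the adherence section and the Discussion around one statement: a single calendar window after week 12, counted from randomisation, applies to both arms regardless of sessions completed. Early stoppers who remain in the study are then measured in that window, with the time since their last session recorded.

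Within the window, require at least 48 h since the last trial session before every post-intervention measure, not only VO2max. Apply the same minimum since the last compulsory PE class in both arms where feasible. Take bloods, blood pressure, body composition and questionnaires before the graded exercise test.

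The cost is a short amendment and tighter booking in the final assessment week. Sample size, intervention and analysis model are unchanged.

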## Methods and analysis

### Study design

This study is the first experiment within a prospectively planned, multiphase randomized controlled trial program and is designed as a two-arm, parallel-group, superiority trial with 1:1 allocation, blinded outcome assessment, and blinded data analysis. The trial is registered under an overarching Chinese Clinical Trial Registry record (ChiCTR2500106549), which includes six prespecified experiments conducted under a single registration number and a shared prespecified outcome framework. Within this registered program, the recruitment dates reported in the registry refer to the recruitment period for the present experiment described in this protocol. The present experiment is designed to evaluate the effects of a 12-week ES intervention on physical and mental health outcomes in sedentary university students. Subsequent experiments within the registered program will be recruited separately in accordance with their respective protocols and prespecified eligibility procedures. Participants allocated to the ES group will undertake a 12-week progressive stair-climbing intervention. During the trial period, control participants will maintain their usual lifestyle and complete the same scheduled assessments. The protocol was developed in accordance with the SPIRIT 2025 statement (**Figure 1**; Additional file 1) (43), and the participant flow diagram is presented in **Figure 2**.

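### The 48–72 h rule for the ES arm's VO2max test cannot be squared with the common assessment window for participants who stop before the end of week 12, and the protocol does not say which rule prevails

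*Protocol article*

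**What the plan says.** VO2max is the single primary outcome. Four places in the protocol article bear on when it is measured after the intervention.

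- **Participant timeline, session anchor.** The rule opens with "For participants in the ES group, post-intervention VO_2_max assessment will be scheduled", so it covers one arm only. It reads: "post-intervention VO_2_max assessment will be scheduled 48–72 h after the final completed intervention session, including any make-up session". The anchor is thus the last session the participant completed, which need not be the last session scheduled. The interval is to be recorded.
- **Participant timeline, calendar bound.** "Each assessment phase will be completed within one week to minimize temporal variation in outcome measurement". This is not specific to either arm.
- **Strategies to improve adherence to interventions.** "Make-up sessions will be arranged within the weekly training schedule and will not alter the prespecified post-intervention assessment window".
- **Study design.** Over the trial period, "control participants will maintain their usual lifestyle and complete the same scheduled assessments". No week is named for the control VO2max test.

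The limitations paragraph of the Discussion expects final examinations to disturb training and adherence. It offers as reassurance that "post-intervention VO_2_max assessment will be standardized according to the final completed intervention session". Under Statistical methods, "The primary analysis will follow the intention-to-treat principle", with ANCOVA of post-intervention VO2max on group and baseline VO2max.

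**The concern.** The last completed session is an event after randomisation, and its date depends on how well the participant adhered. Tying the primary measurement to it in one arm makes follow-up time a function of adherence in that arm, while the other arm has no such link. An intention-to-treat comparison of a 12-week programme needs both arms measured at a comparable time after randomisation, whether or not training continued.

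Two things could go wrong for an ES participant who stops early or misses the final weeks:

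- **Anchor followed.** The test takes place two to three days after the last training, in whatever week that was. If fitness gained by then would have faded by the end of the 12 weeks, the early value flatters the ES arm.
- **Window followed.** The 48–72 h rule is broken. Staff may test anyway, or may treat the participant as having no valid slot. A value recorded as missing would be multiply imputed from group, baseline outcome and other baseline predictors. The article names no adherence variable in that model.

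Baseline adjustment and blinded assessors do not repair unequal timing, and a mistimed test cannot be repeated later.

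**Working it through.** **1. The plan's own sample-size figure.** It does not depend on test timing but supplies the scale. Inputs from the Sample size section: group SDs 3.87 and 4.95, target difference 3.5, two-sided alpha 0.05, power 80%, attrition 10%.

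- Pooled SD = √[(3.87² + 4.95²)/2] = 4.44, so d = 3.5/4.44 = 0.79.
- The normal approximation gives 26 per group. The noncentral t gives 26.15 at d = 0.79, with power 0.798 at 26. The stated 26 is reproduced within rounding.
- 26/0.90 = 28.9, so 29 after attrition, with 30 planned.

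**2. When the test falls due under the anchor.** Take randomisation as day 0 and a last session at the end of week L as day 7L. The test is due on days 7L + 2 to 7L + 3.

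| Last completed session | Test due (day) | Days before a week-12 finisher |
|---|---|---|
| End of week 12 | 86–87 | 0 |
| End of week 11 | 79–80 | 7 |
| End of week 10 | 72–73 | 14 |
| End of week 8 | 58–59 | 28 |
| End of week 6 | 44–45 | 42 |

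**3. Can one week hold both?** On the most generous placing, a seven-day window running from day 80 to day 86 just contains a week-11 stopper and a week-12 finisher. For any larger gap no single week holds both. If the window opens only once the 12 weeks are over (day 85 on), a test within 72 h requires a last session on day 82 or later, so the conflict starts sooner. Make-up sessions do not resolve it. They stay inside the weekly schedule and "will not alter the prespecified post-intervention assessment window", so they cannot stand in for missed final weeks.

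**4. Who is affected.** Participants who train to the end of week 12, including by make-up sessions that week, satisfy every rule. The conflict is confined to ES participants whose last session is materially earlier and who still attend testing. The documents give no rate for this group. They do foresee exam-week disruption, discontinuation of the intervention after a serious adverse event, and runs of three missed sessions.

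**5. Size, on assumed figures only.** Shift in the mean difference = share of the ES arm tested off schedule × (off-schedule value − on-schedule value).

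- *Simple grid.* Shares of 10–30% and individual differences of 0.5–1.75 mL/kg/min give from 0.10 × 0.5 = 0.05 to 0.30 × 1.75 = 0.53.
- *Gain and decay.* Assume the gain rises linearly to 3.5 at week 12, stopping times are uniform over weeks 2–11, and the detraining half-life is 2, 4 or 6 weeks. The mean gain at an early test is 3.5 × 6.5/12 = 1.90. The same people would average 0.54, 0.95 or 1.17 at week 12. The shift is 0.07–0.14 at a 10% share, 0.14–0.27 at 20% and 0.22–0.41 at 30%.

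For scale, the unadjusted standard error with 30 per arm is 4.44 × √(2/30) = 1.15.

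**The case against.** The strongest reply is that the anchor should not be read alone. The test is described as post-intervention, the intervention lasts 12 weeks, the sentence before the anchor asks for a one-week phase, and the adherence section speaks of a prespecified window. Read together, 48–72 h is a spacing rule inside an end-of-trial window, intended to keep the test clear of the last or made-up session. The actual interval is recorded, so departures will be visible. A condensed article may also leave the handling of early stoppers to a fuller protocol.

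Much of this stands. A reader might infer that early stoppers will routinely be tested in, say, week 6 while controls are tested at week 12. The documents do not support that. No section orders an early test, the one-week phase and the prespecified window point against it, and a week-12 control test is only an inference from the shared assessment schedule. Nor can the 10% attrition allowance serve as the share tested early. It describes participants lost to the analysis, not participants measured at the wrong time. In the gain-and-decay illustration the bias is proportional to the true gain, so under that model it could not create an effect where none exists.

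What does not stand is that the text already resolves the matter. The rule is written on the last completed session, has no exception for those who stop, and is the very device the Discussion relies on when training is disrupted. The one-week sentence could even be read as a limit on each participant's own test battery, in which case it would not prevent an early test. This is a conflict between stated rules, not a detail left out.

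**Conclusion.** The point holds as an unreconciled conflict in the timing of the primary outcome. It is not a demonstrated difference in follow-up between arms. For ES participants whose last session falls more than about a week before the end of week 12, the session anchor and a common one-week window cannot both be met, and the protocol names no order of precedence. One resolution makes timing depend on adherence in one arm; the other breaks the 48–72 h rule and may cost a valid test.

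The size of any bias cannot be computed, because the documents give neither a rate of early stopping nor a time course for VO2max. On the assumed figures it is probably a few tenths of a mL/kg/min or less. The most extreme corner of the grid, 0.53, is 15% of the 3.5 target and less than half of one standard error. Severity is moderate. The case for acting rests on the contradiction and on how cheaply it can be removed before outcome testing, not on a large number.

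**What to change.** Reconcile the Participant timeline, the adherence section and the Discussion around one rule:

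- Set a single post-intervention VO2max window by time since randomisation, at the scheduled end of the 12-week period, for all randomised participants in both arms.
- Treat the interval since the last session as a minimum spacing within that window, with no upper limit for participants who have stopped training. Keep recording the actual interval.
- State that participants who stop training without withdrawing consent are still tested in that window and are included in the intention-to-treat analysis.
- Reword the Discussion so that the common window, not the last completed session, is what standardises the test.

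The cost is a few sentences and a protocol amendment, with no extra visits, staff or participants. The one drawback is a more variable interval since last exercise among non-adherent ES participants, which an intention-to-treat comparison should reflect in any case.
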